**3.1 SIGNIFICANCE**

**HIV continues to disproportionately affect Black communities in the US.** Current epidemiologic data indicate that Blacks represent 45% of all new HIV infections, while representing 14% of the U.S. population.^1^ Most new HIV infections among Blacks have been observed in men who have sex with men (MSM). The estimated range of MSM representation in new HIV infections among Black males is 63%-66%^22^; the distribution of new HIV infections among Black MSM is increasing, with those younger than 25 years of age accounting for over half of the new infections via condomless anal intercourse (CAI) with other Black males (homophily)^1^; however, likelihood of engagement in HIV risk is influenced by a variety of socioecological factors.^23-29^

**Socioecological factors structure vulnerability to HIV infection risk for many Black MSM.**^29-32^ Some Black MSM seek refuge from environments that disaffirmed and/or attempted to dismantle essential aspects of their personhood, including their gender expression(s) and sexualities.^7,33^ Nonetheless, exposure to disaffirming environments has been reported to have residual negative psychosocial impacts.^34-36^ In our previous work, we found that early-life (before age 18) exposure to environments that disaffirmed same-sex behaviors was associated with increased number of sex partners and HIV infection in adulthood.^37^ In another study,^38^, we also found that financial crisis was associated with >2 male sexual partners in the past 6 months (OR=1.65; 95%CI 1.18–2.29), recent conviction was associated with sexually transmitted infection (STI) at 6-months (OR=3.97; 95%CI 1.58–9.94), and unstable housing was associated with an STI at 12-months (OR=1.71; 95%CI 1.02 = 2.86). The absence of “behavioral risk factors” does not confer protection against other economic and social hardships that still exert influence on HIV outcomes for Black MSM. It is therefore necessary to identify and strengthen assets to support resilience to hardships that can undermine the effects of HIV interventions.

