Our working hypotheses are that the *OFOV* intervention will increase uptake of HIV testing and PrEP use (for HIV-negative family members) and linkage to care and treatment engagement (for PLHIV who were not in care at baseline). We will measure frequency of HIV testing at 3- and 6-months post-intervention using a combination of online self-report survey and verification by through clinic medical records. We will seek to obtain medical records releases from participants to obtain data on HIV testing, PrEP prescription, engagement in care and ARV use. Our secondary hypotheses are that *OFOV* will increase the number of family-based assets, resilience and reduce number of sex partners and frequency of CAI for members who are not in mutually monogamous relationship with an HIV-negative or virally suppressed partner. We also measure intersectional stigma and asset-impact indicators at all time points (to characterize these in our sample) ^102,103^ Families in the waitlist SOC control arm have the option to participate in OFOV after 6-month data collection.

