**3.6.2 Procedures**

**3.6.2A Recruitment and Sample****.** We will recruit six HBC families (n=100). See Human Subjects section *4.4. Statistical Design and Power* for sample size and power calculations. We will conduct recruitment using three methods. First, we will disseminate recruitment/marketing materials via **The Federation**, **HLM** and **The Coalition’s** online communication platforms. Potential participating families can contact the study office directly via text message or phone call in response to marketing materials. Second, we will recruit through receipt of referrals of interested families from **The Federation**, **HLM** and **The Coalition’s** programs and outreach activities. Research staff have extensive experience engaging MSM for research and program activities. Third, we will also rely on word-of-mouth as a mechanism through which families become aware of the study and contact us.

**3.6.2B Inclusion/Exclusion Criteria.** Eligibility for the study will be determined primarily at the family-level. At least 12 members of the same HBC family must be willing to participate together, of which at least half the participating members must be Black MSM. Participating family members must reside in the New York City metro area. Black MSM participants must be at least 18 years old. [name], who is a pediatric HIV specialist, believes that the social risk of a confidentiality breach to the biological family is heightened for youth under the legal age of emancipation. Furthermore, we could not justify the risk of enrolling people younger than 18 since our research aim can reasonably be addressed without their inclusion. In addition, Black MSM must also currently self-identify as cisgender or transgender man, report anal sex with another man at least once within the previous six months (note: other HBC family members can identify as any gender).

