**3.6.4C Primary and Secondary Outcomes.** Our primary outcomes will be HIV testing and PrEP use (for HIV-negative or unknown members) or “In HIV care” and “currently on HIV treatment” (for PLHIV) within 6 months of randomization. For HIV-negative MSM we will also record the frequency of HIV testing over the prior 3-months, but we anticipate that few participants will take >1 test in this short period of time. A detailed summary of primary outcome measures is included in Table 3. Our secondary outcomes (see also Table 4) will be number of family-based assets, resilience, number of sexual partners, and relative frequency of CAI. We will also assess sense of community^105^ at all time-points. In our previous research with Black MSM we found that sense of community was associated with increased condom use for anal intercourse (*OR*=1.26, 95%CI 1.05,1.52; p<.05).^14^

**3.6.4D Implementation Outcomes.** We will assess feasibility and acceptability of *OFOV* using a combination of process measures (e.g., intervention completion rate) and validated scales (e.g., peer support evaluation inventory). Implementation outcomes measures are also summarized in Table 4.

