The likelihood of intervention contamination across the study groups could not be excluded, because some participants may not receive the respective interventions to which they are randomized, e.g., some members of the control group may end up in situations in which they receive some level of support from a HBC family in the intervention group. Therefore, we will also perform per-protocol analysis, which includes only those participants who strictly adhered to the protocol and report the results along with the results of the ITT analyses.

| **Table 4. Summary of RCT Phase Measures** | |
| --- | --- |
| **Construct** | **Sample Items and reliability** |
| **HIV Testing** (self-report and medical record verified) | Number of HIV tests in past 3-months |
| **PrEP Use** (self-report and medical record verified) | Is participant currently on antiretrovirals for HIV PrEP? |
| **In HIV Care** (self-report and medical record verified) | Has participant attended HIV medical appointment in past 3-months |
| **On HIV Treatment** (self-report and medical record) | Is participant currently on antiretrovirals for HIV treatment? |
| **Condomless anal intercourse** (past 3 months) | Relative frequency = # times condoms used during anal sex / total # episodes of anal sex |
| **Number of sexual partners** | Total number of sexual partners in the past 3 months |
| **Sense of Community Scale^105^** (8-items) | I feel like I am a member of my house family (α=0.87 - 0.92) |
| **Brief Resilience Scale^106^** (6-items) | I tend to bounce back quickly after hard times? (α=0.80-0.91) |
| **READY Tool** (24-items)^102,103^ | My family expects me to try my best. I ask my family questions to get ideas. (α=0.85) |
| **Asset Inventory (40-items)^21^** | I seek advice and counsel from my parents. My family has clear rules and consequences. |
| **Intersectional Stigma (Latent Variable)** |  |
| **HIV Stigma Scale^107^** | |
| *Enacted subscale (10-items)* | Has a healthcare worker not wanted to touch you because you have HIV? (α=0.92) |
| *Vicarious subscale (10-items)* | How often have you heard stories about someone with HIV being refused care? (α=0.88) |
| *Perceived subscale (10-items)* | In your community, how many people think a person with HIV is disgusting? (α=0.94) |
| *Internalized subscale (10-items)* | How often do you feel guilty about having HIV? (α=0.83) |

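### Table 4 defines the condomless anal intercourse outcome as the proportion of acts with a condom, the exact complement of the outcome it labels

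*Protocol*

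**What the plan says.** Protocol section 3.1 introduces the abbreviation as "condomless anal intercourse (CAI) with other Black males", so CAI means acts without a condom. Section 3.4.1 lists its relative frequency among the status-neutral secondary outcomes, and section 3.6.4C repeats the list: "number of family-based assets, resilience, number of sexual partners, and relative frequency of CAI". Section 3.6.1 gives the expected direction: the intervention is to "reduce number of sex partners and frequency of CAI for members who are not in mutually monogamous relationship" with an HIV-negative or virally suppressed partner.

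Table 4 turns this into a measure. The row carries the condomless anal intercourse label and a 3-month recall window, and its definition reads "Relative frequency = # times condoms used during anal sex / total # episodes of anal sex". The protocol nowhere says that this score is to be reversed or subtracted from 1.

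Two eligibility rules in section 3.6.2B bear on the denominator. Black MSM must "report anal sex with another man at least once within the previous six months". For each family, "at least half the participating members must be Black MSM"; the anal sex criterion is not applied to the other members.

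**The concern.** The label, the named outcome and the hypothesis all refer to acts without a condom. The formula counts acts with one. Anyone who programs the formula and reports the result under the row's label will have the sign of the effect backwards.

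Nothing in the output would reveal it. The written score and the intended one both run from 0 to 1. Because one is a constant minus the other, they have the same variance, so a difference between arms keeps its size and standard error and changes only its sign.

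Section 3.4.1 says that the trial data will be used to estimate the effect on this outcome, and section 3.7 says that the pilot findings will shape the protocol for a full cluster trial. A reversed estimate could therefore be carried into that planning. If the reversal were noticed only once the data were in, correcting it would mean redefining a named outcome after seeing the results.

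**Working it through.** The protocol gives no numerical figure for this outcome, so there is nothing to reproduce. The check is algebra on the written definition.

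**Notation.** For one participant over 3 months, C is the number of anal sex episodes in which a condom was used and T is the total number of episodes.

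- Written in Table 4: C / T
- Named by the label and by sections 3.4.1 and 3.6.4C: (T − C) / T = 1 − C / T

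The written score is the exact complement of the labelled one.

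**Effect on a comparison.** Let p₁ and p₀ be the mean CAI proportions under the intervention and the control. The true difference is p₁ − p₀. The written formula gives (1 − p₁) − (1 − p₀) = −(p₁ − p₀): the same size with the opposite sign.

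**Values.** The counts are assumed for illustration and do not come from the protocol.

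| Case | C | T | As written, C/T | As labelled, (T − C)/T |
|---|---|---|---|---|
| Lower condom use | 4 | 10 | 0.40 | 0.60 |
| Higher condom use | 7 | 10 | 0.70 | 0.30 |
| Never uses condoms | 0 | 10 | 0.00 | 1.00 |
| Always uses condoms | 10 | 10 | 1.00 | 0.00 |
| No anal sex in the window | 0 | 0 | undefined | undefined |

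From the first row to the second, the labelled quantity changes by 0.30 − 0.60 = −0.30 and the written one by 0.70 − 0.40 = +0.30.

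**Zero denominator.** The last row shows that correcting the numerator leaves T = 0 undefined. The eligibility rules make this possible in two ways. A Black MSM participant may qualify on anal sex 3 to 6 months ago and have none in the 3-month window. Other members need not report anal sex at all. With 100 participants and at least half of each family Black MSM, at most 100 × 0.5 = 50 members fall outside the anal sex criterion. That is a ceiling on members without the criterion, not an estimate of how many scores will be undefined.

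**The case against.** The strongest reply is that this is a slip in a table, on one of several secondary outcomes, in a six-family pilot. The printed formula is visible to whoever writes the analysis code; a careful analyst would take 1 minus the value, and no data would be lost. This stands as far as consequence goes: a reversed report is a risk and not a certainty, and it can be undone. It does not remove the error, because the protocol chose to state a formula and that formula contradicts its own label and hypothesis. It is not a detail left for a statistical analysis plan; a plan that copied the line would inherit the reversal.

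A reader might infer more than the protocol supports:

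- **Bias from dropping participants with no anal sex.** The protocol does not say that they will be dropped. Section 3.6.5 commits to analysis as assigned, and the rule for a zero denominator is ordinary analysis-plan material.
- **Half the sample undefined.** The protocol gives no rate of abstinence. Members who are not Black MSM may be of any gender and may well report anal sex. The ceiling of 50 also leaves out Black MSM with none in the last 3 months, so it does not bound the number of undefined scores.
- **A subgroup defined after randomisation.** Section 3.6.1 limits the hypothesis to members outside mutually monogamous relationships, while section 3.6.4C and Table 4 list the measure briefly without that limit. Nothing says that status after randomisation will be used, and section 3.6.4B lists relationship status among the baseline characteristics.
- **A specific inflated ratio.** Section 3.6.5 specifies relative risks for the binary outcomes only. No ratio is planned for CAI, so any ratio would rest on assumed inputs. Only the reversal of direction is established.

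**Conclusion.** The Table 4 definition is wrong as written. It measures the proportion of protected acts under a label, an outcome name and a hypothesis that all concern unprotected acts. If it is applied literally, the estimated effect on the CAI proportion has the right size and the wrong sign, so benefit reads as harm and harm as benefit. This follows from the text alone and needs no assumption about the data; only the counts in the illustration are assumed.

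The reach is limited. HIV testing, PrEP use, HIV care and ARV treatment are untouched, as is the sample size. The undefined ratio for participants with no anal sex in the window is a secondary note and not part of the error. The line should be corrected before any analysis is programmed.

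**What to change.** Choose one of two equivalent corrections in Table 4:

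1. Keep the label and change the numerator: relative frequency of CAI = (total anal sex episodes − episodes with a condom) / total anal sex episodes, past 3 months.
2. Keep the formula, rename the row as condom use during anal sex, and state in sections 3.4.1, 3.6.1 and 3.6.4C that the outcome is condom use and that an increase is expected.

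The first is the smaller edit, because the rest of the protocol already speaks of CAI. It costs one line in the table and one in the analysis code. Both counts are already required by the written formula, so no survey item changes.

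As an optional addition, report the count of condomless acts (T − C, equal to 0 for those with no anal sex) beside the ratio as a supportive analysis. It is defined for every participant who answers and needs no further data. It measures a different quantity from the relative frequency, so it should accompany that outcome and not replace it.
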